### Design and setting

The study is a pragmatic multicentre feasibility study taking place in 5–8 GP practices in Cambridgeshire and Peterborough, England, UK. Fig 1 shows the study schedule (SPIRIT).

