#### Participant recruitment.

Eligible women are identified through searches of the electronic health records at General Practices based on the inclusion and exclusion criteria above. To prevent including women who may reach the age of 50 years between the searches being completed and receiving the invitations (see ‘Processes and Interventions’ section below), the search includes women aged 40–48 years. Depending on the population size of each practice, recruitment rate, and overall uptake into the study, either all or a random sample of those women who meet the eligibility criteria are invited to take part in the study. Invitations are staggered in random order. Those women are sent an invitation letter and S3 Participant information sheet by post. A reminder letter is sent by post two to four weeks later to those women who have not completed the consent form.

Women can complete the online written consent form which includes a screening question about breast cancer susceptibility gene already identified within their family. Those answering yes to this screening question are advised to make an appointment to discuss their breast cancer risk with their GP and are not able to continue with the study. After providing online written consent, all participants are asked to complete a short baseline questionnaire (details below) hosted online. On completion of the baseline questionnaire, participants are asked to provide data for a breast cancer risk assessment.

Recruitment opened on the 28^th^ of November 2024 for a duration of 8 months (until the 30^th^ of June 2025) or until 1,000 women have been recruited, whichever happens first.

Participant recruitment and flow through the study is summarised in Fig 2.

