**Moderators**				
Numeracy [28]	•			
Health literacy [29]	•			
Beliefs about breast cancer [30]	•			
Time orientation [31]	•			
Intolerance of uncertainty [32]	•			

Table 2 specifies all measures, instruments and data collection points (baseline and at 1, 3 and 6 months after receiving the risk assessment results). All outcomes will be measured by self-report and include risk perception, psychological impacts of the risk assessment, lifestyle and behaviour, and actions taken following the risk assessment. Risk perception will be assessed using questions about absolute and comparative risk, risk conviction and recall of risk. Psychological measures include cancer-related worry, anxiety and quality of life using the Lerman cancer worry scale [21], the short-form of the state scale of the Spielberger State Trait Anxiety Inventory (STAI) [22] and the EQ-5D-5L [23, 24] respectively. These have been chosen as the Lerman cancer worry scale and short-form STAI have been widely used in the literature and so will allow comparison with other studies, and the EQ-5D-5L is the recommended measure for use in economic analyses by NICE [25]. We will also collect data on: motivations and concerns regarding participation in the study using multiple choice questions and short open text boxes questions; the acceptability of the study using 5-point Likert scale questions [26]; the impact of cancer risk assessment using the MICRA scale [27]; satisfaction with the test using 5-point Likert scale; questions assessing the degree of satisfaction with the multifactorial cancer risk assessment; views on the risk information using 5-point Likert scale questions assessing the information in the CanRisk report; views on the GP consultation, including assessing the usefulness of the consultation and whether the appointment clarified understanding of breast cancer risk. Additionally, patients who agree to have their appointment recorded will receive an optional survey immediately after their GP consultation exploring their experience of the appointment. Attitudes towards risk management options (i.e., earlier or more frequent screening, medication and surgery) will also be measured via standardised scales and multiple-choice questions reviewed by patient and public partners. Lifestyle and behavioural data will be collected through multiple choice questions; these will include question about current behaviour regarding breast self-examination, intention to attend screening, change in behaviour (i.e., weight, alcohol consumption and exercise) and healthcare utilisation (i.e., number and type of contact) specifically focusing on breast health in the six months prior to baseline and six months after baseline. Data on actions following the risk assessment will only be collected for women found to be at increased risk and if they have attended the GP appointment. Actions measured will include multiple choice questions about the attendance at the GP appointment (or intention if not done) as part of the study and uptake (or intention if not done) of risk reduction strategies (i.e., earlier or more frequent screening, medication and surgery). We will also collect data on numeracy [28], health literacy [29], beliefs about breast cancer [30], time orientation [31], and intolerance of uncertainty [32]. These will be considered as moderators for the measures above that will help test interactions between variables in the study.

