#### Psychological and behavioural impact of multifactorial breast cancer risk assessment.

For continuous outcomes (anxiety, worry, risk perception, recall of risk information, and intentions) analysis of covariance will be used to calculate change at each follow-up within each risk group, adjusting for clustering between each GP practice. Any differences between the risk groups on analysis of covariance will be tested using an F-test, followed by estimation of the comparison between those at near population level risk and those at moderate or high risk based on the CanRisk assessment. All models will be adjusted for age, ethnicity, education level, deprivation, baseline EQ-5D and general practice. The size of the change between groups will be interpreted by comparison with the standard deviation (SD), with the criteria for clinically relevant change being a change of 0.5 SD [29]. We will also test for interactions between the risk groups and age, family history of breast cancer, numeracy, beliefs about breast cancer, time orientation, intolerance of uncertainty and responding “not anxious or depressed” versus “slightly/moderately/severely or extremely anxious or depressed” on EQ-5D at baseline. Analyses will be repeated within the subgroups where the p value for interaction is < 0.05.

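### If the baseline-anxiety interaction triggers subgroup re-analysis, change from baseline in those subgroups will carry regression to the mean, which the design cannot separate from an effect of the risk result

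*Protocol article*

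**What the plan says.** All of the analysis text is in the Protocol article, under Psychological and behavioural impact of multifactorial breast cancer risk assessment.

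- The first quantity is within-group change: "analysis of covariance will be used to calculate change at each follow-up within each risk group". A comparison between near-population and moderate/high risk follows.
- Moderators are then tested: "We will also test for interactions between the risk groups and age, family history of breast cancer", and five others. The last of the seven is "responding “not anxious or depressed” versus “slightly/moderately/severely or extremely anxious or depressed” on EQ-5D at baseline".
- The rule for subgroups is "Analyses will be repeated within the subgroups where the p value for interaction is < 0.05".

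The anxiety outcome is the short state form of the STAI (Study outcomes and measures, text below Table 2). Measures are taken at "baseline and at 1, 3 and 6 months after receiving the risk assessment results". There is one baseline occasion: "After providing online written consent, all participants are asked to complete a short baseline questionnaire" (Participant recruitment).

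On design, "The study is a pragmatic multicentre feasibility study taking place in 5–8 GP practices" (Design and setting), and every participant is offered the assessment. The non-participating practices named under Study outcomes and measures serve only the comparison of the proportion of women identified at moderate or high risk. They supply no psychological data.

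**The concern.** Women who report anxiety or depression at baseline are partly women with lasting anxiety and partly women caught at a bad moment. The second part fades by follow-up whatever the risk result says, so the mean STAI of this subgroup falls. The mean of the women who reported none drifts up for the same reason. Change from baseline in either subgroup mixes this drift with any effect of the result. Without a second baseline or an untreated group, the study data cannot separate the two.

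The direction is unhelpful. Women already anxious are those in whom a rise after a risk result would matter most, and the drift works towards showing a fall in them. The sample-size section presents change in anxiety or worry within each risk group as something the study is sized to detect, so readers are likely to look at the same quantity in subgroups.

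**Working it through.** **Step 1: the plan's own figure.** The Sample size section claims 90% power at p < 0.05 for a 0.5 SD change, with 40% loss, in both risk groups. Followed-up numbers are 170 × 0.6 = 102 (moderate/high) and 830 × 0.6 = 498 (near-population). With baseline to follow-up correlation r (not given, so varied) and a two-sided test (assumed), power = Φ(0.5√n / √(2(1−r)) − 1.96).

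- n = 102, r = 0: 0.5 × 10.10 / 1.414 = 3.57, so Φ(1.61) = 94.6%.
- n = 102, r = 0.5: 5.05 − 1.96 = 3.09, so 99.9%.
- n = 498: above 99.9% in both cases.

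The 90% holds as a minimum and is not in dispute.

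**Step 2: formula for the artefact.** Let p be the share anxious at baseline, c the normal cut-point for that share, φ the standard normal density, and ρ0 and ρ1 the correlations of the EQ-5D item's underlying score with baseline and follow-up STAI. With no true effect, in STAI SD units:

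- anxious subgroup: change = −(ρ0 − ρ1) φ(c) / p
- non-anxious subgroup: change = +(ρ0 − ρ1) φ(c) / (1 − p)

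The documents give none of p, ρ0, ρ1 or the STAI retest correlation r. All are assumptions.

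**Step 3: central case.** Take p = 0.40, ρ0 = 0.65, ρ1 = 0.45, r = 0.60. Then c = 0.253 and φ(c) = 0.386.

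- Anxious: −0.20 × 0.386 / 0.40 = −0.19 SD.
- Non-anxious: +0.20 × 0.386 / 0.60 = +0.13 SD.

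A simulation of 1,000,000 women with no effect gave −0.196 and +0.130 SD, and −0.001 SD in the whole sample. Refitting ANCOVA inside each subgroup with baseline STAI as a covariate gave the same −0.196 and +0.130, so that adjustment does not remove the drift. The contrast between risk groups inside each subgroup was within 0.01 SD of zero.

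**Step 4: range.** If the item relates to follow-up STAI only through same-day STAI, the correlation decays fully, to ρ1 = ρ0 × r. The range below takes p = 0.25 to 0.50, ρ0 = 0.50 to 0.65, r = 0.5 to 0.7, and at least half of that decay.

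- Anxious, smallest: p = 0.50, drop 0.50 × 0.3 × 0.5 = 0.075; 0.075 × 0.399 / 0.50 = 0.06, so −0.06 SD.
- Anxious, largest: p = 0.25, drop 0.65 × 0.5 = 0.325; 0.325 × 0.318 / 0.25 = 0.41, so −0.41 SD.
- Non-anxious, smallest: p = 0.25, drop 0.075; 0.075 × 0.318 / 0.75 = +0.03 SD.
- Non-anxious, largest: p = 0.50, drop 0.325; 0.325 × 0.399 / 0.50 = +0.26 SD.
- If ρ1 = ρ0, both are zero (simulated −0.002 and −0.001).

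**Step 5: chance of a nominally significant change in the central case.** The SD of change is √(2 × 0.4) = 0.894. For n = 199 (498 × 0.4), z = 0.193 / 0.894 × √199 = 3.05, so the chance is Φ(3.05 − 1.96) = 86%. The same formula gives:

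| Subgroup | Risk group | n | Chance |
|---|---|---|---|
| Anxious | near-population | 199 | 86% |
| Anxious | moderate/high | 41 | 28% |
| Non-anxious | near-population | 299 | 70% |
| Non-anxious | moderate/high | 61 | 20% |

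These rates take the re-analysis as carried out. They ignore clustering and any selection that the trigger itself introduces.

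**Step 6: the trigger.** Simulating 4,000 studies of 600 followed women with no effect, the interaction test reached p < 0.05 in 4.7%. The drift is common to both risk groups, so it does not raise the trigger rate. If anxiety and worry are each tested at three follow-ups (six tests), the chance of at least one false trigger lies between 5% (fully correlated) and 1 − 0.95^6 = 26% (independent).

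**The case against.** - **The re-analysis is conditional.** A reader might infer from the rates in Step 5 that most studies run to this plan would report false improvement in anxious women. The documents do not support that: with no effect, about 5% of individual tests reach the re-analysis. It would also be reached when anxious women truly respond differently, and their change estimate would then be read most closely.
- **The sentence is open to a milder reading.** A significant interaction between risk group and moderator most naturally leads to the risk-group comparison within each subgroup, which is sound. This stands in part. But the text repeats the analyses without restriction, and the first of them is within-group change.
- **The 0.5 SD criterion.** A reader might infer that subgroup change will be judged against 0.5 SD. The analysis section ties that criterion to change between groups, which is not biased here. The Sample size section applies 0.5 SD to change within whole risk groups, not within moderator subgroups.
- **The inputs are assumed.** The cut uses one item mixing anxiety with depression, on a different instrument from the outcome. That is why partial decay is allowed in the range, and why zero remains possible.
- **Worry was not computed.** A general anxiety/depression item need not relate to cancer-specific worry as strongly as to the STAI.
- **The stakes are limited.** This is one of seven moderators in a feasibility study, and none of its three numerical progression criteria depends on it. That argues for a small repair, not for leaving the text as it is.

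**Conclusion.** The concern holds in a conditional and limited form. If the interaction with baseline EQ-5D anxiety/depression reaches p < 0.05, the text allows change from baseline to be re-estimated in subgroups where regression to the mean has a predictable direction and no control. None of the assumed scenarios reaches 0.5 SD by the artefact alone. In the central case it is still enough to make a true 0.20 SD rise among anxious women look like no change.

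The size rests entirely on assumed correlations and prevalence, and applies to the STAI only. It would be wrong to extend the point to the moderate/high versus near-population contrast or to whole-sample change within risk groups. Women are not selected on anxiety for the latter, and both came out essentially unbiased in the check.

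**What to change.** Add one sentence to the analysis section. For anxiety and, as a precaution, worry, baseline EQ-5D anxiety/depression is used only as a moderator of the moderate/high versus near-population contrast at each follow-up. That contrast is estimated in one model on all participants, with the interaction term and the outcome's own baseline value. Change from baseline within subgroups defined by this item is not interpreted as an effect of the risk assessment, and within-risk-group change is kept for the whole sample.

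The change needs no new data, visits or participants and stays in the same model family. Its cost is that the contrast alone cannot show a rise common to both risk groups among anxious women. The uncontrolled pre-post estimate cannot show that reliably either, so little of value is given up.

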#### Process evaluation.

Qualitative data from semi-structured interviews will be analysed using inductive and deductive thematic analysis [36]. All interviews will be audio recorded and transcribed verbatim before analysis. The inductive analysis will look for emergent themes relevant to the study aims and the deductive thematic analysis will be organised around the seven dimensions of the Theoretical Framework of Acceptability [13]. According to this framework, acceptability is defined as a “multi-faceted construct that reflects the extent to which people delivering or receiving a healthcare intervention consider it to be appropriate, based on anticipated or experienced cognitive and emotional responses to the intervention” [13]. Findings from interviews with participants, non-participants and clinicians will be compared, looking for concordant and discordant themes. A fidelity checklist based on the training provided to GPs will be used alongside the video recordings from healthcare appointments to assess the adherence of GPs to the protocol during consultations with women at moderate or high risk. Verbatim transcriptions from the audio of the video recordings will be analysed qualitatively using thematic analysis to explore challenges and strengths in GP communication, patient reactions, and patient-clinician dynamics. Coding will be performed deductively by two independent researchers.

Descriptive statistics will be used to analyse the results from the questionnaires. Content analysis will be used to analyse the short open text responses from non-participants (women and practice managers and or research leads).

#### Economic analysis.

Unit costs from published sources [37–39] will be applied to healthcare utilisation data and used to calculate costs per participant in the 6 months before and the 6 months after baseline. This includes the time and costs associated with using the cancer risk assessment. Costs and resource use will be reported as means, standard deviations, medians, and interquartile ranges. Data from the study will be applied to an existing cost-effectiveness model [40] to evaluate the cost-effectiveness of the intervention.

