#### Breast cancer risk assessment.

Personalised risk estimates are generated using the CanRisk tool. Population-based studies have shown that BOADICEA, including incorporation of polygenic scores, has moderate-to-good discrimination with AUCs or c-indices of 0.68–0.69 in women aged less than 50 years or those who are premenopausal [3,17] and is well calibrated with a ratio of expected to observed number of cases (E/O) of 0.97 [17].

For this study, personalised risk estimates are calculated based on family history, demographic, lifestyle and hormonal factors in addition to a PGS based on 309 common genetic variants [18]. Data on family history, lifestyle and hormonal factors is collected via the MyCanRisk app. Women receive a link to the MyCanRisk app after completing the consent and baseline questionnaire. MyCanRisk is a platform independent Progressive Web App that supports the on- and off-line collection of personal risk factor information alongside the detailed family history required to conduct a CanRisk calculation.

Participants have the option not to have PGS testing. For those participants consenting to this element of the study receive a saliva sampling kit on the post. The returned kits are collated by the research team and sent in batches for analysis by a clinically accredited laboratory. DNA samples which pass quality control are genotyped using a genome-wide array, specifically the Illumina Global Screening v4 Array (GSAv4). These data are then used (in conjunction with imputation to a reference panel to estimate genotypes for SNPs not on the array) to compute the 309 SNP PGS. The data is then sent to the bioinformatics provider for PGS analysis. The data is also used to estimate genetic ancestry: this enables the PGS to be standardised to the appropriate population and the use of ethnicity-specific BOADICEA model within CanRisk [19]. These results will then be returned to the research team.

The research team incorporates the PGS results together with the data on family history, lifestyle and hormonal factors collected via MyCanRisk, into the CanRisk tool and generate a personalised risk estimate for each participant. For those women opting not to have PGS testing, the personalised risk estimate is based on family history, lifestyle and hormonal factors only.

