
### Data collection

The data collection process is shown in Fig 2.

Participant baseline data is collected via an online questionnaire.

Participant level follow-up data is collected via participant questionnaires at 1, 3 and 6 months after receiving the results letter and from the GP electronic medical records 6 months after the last participant has received the results letter for all individuals who have consented to participate in the study. This includes coded entries relating to breast symptoms, breast cancer risk and, for those at moderate and high risk, uptake of risk-reducing interventions.

Practice-level aggregated data on the age, ethnicity and Index of Multiple Deprivation of all eligible women will be extracted at the end of the study from the GP electronic medical records. Practice-level and aggregated individual level data on the number of referrals of women potentially at above population-level risk for breast cancer and the outcomes of those referrals for all practices across Cambridgeshire and Peterborough for the period of the study will also be extracted from the electronic health records at the clinical genetics clinic at Cambridge University Hospitals NHS Foundation Trust. For the practices participating in this study, the same data will be extracted for the 12 months prior to the study. Data on the number of women registered at each practice will be extracted from publicly available National General Practice profiles.

A mixed-methods process evaluation is being conducted alongside collection of outcome data to explore how proactive breast cancer risk assessment is delivered and perceived at practice and patient levels. The main four questions guiding this element of the study will focus on: 1) whether this feasibility study did what it was set out to do; 2) whether the different elements in the study design worked and why; 3) what the different stakeholders thought about CanRisk and how it was implemented in general practice: and 4) whether implementing CanRisk in general practice is acceptable. Data is collected from women, GPs conducting breast cancer risk consultations, and practice managers and/or research leads from the different research sites. Three sources of data contribute to this process evaluation.

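### Healthcare use and costs are counted over the 6 months after baseline, but follow-up is timed from the results letter, so the costing window matches no collection point and can omit part of the care that follows the result

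*Protocol article*

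**What the plan says.** Two sections tie healthcare use and cost to baseline. Economic analysis says unit costs will be applied to healthcare utilisation data and "used to calculate costs per participant in the 6 months before and the 6 months after baseline". Study outcomes and measures (text under Table 2) describes the healthcare-use questions as "specifically focusing on breast health in the six months prior to baseline and six months after baseline".

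Baseline comes early. Participant recruitment states: "After providing online written consent, all participants are asked to complete a short baseline questionnaire". Only after that do women enter data in MyCanRisk and, if they agree to polygenic score (PGS) testing, receive a saliva kit by post. Breast cancer risk assessment then says: "The returned kits are collated by the research team and sent in batches for analysis by a clinically accredited laboratory". Genotyping, imputation, PGS calculation and the CanRisk run follow before a letter is sent.

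Follow-up uses a different origin. The text under Table 2 gives the "data collection points (baseline and at 1, 3 and 6 months after receiving the risk assessment results", and Data collection refers to "participant questionnaires at 1, 3 and 6 months after receiving the results letter". Table 2 marks healthcare utilisation at baseline and at 6 months only. GP record data are taken "from the GP electronic medical records 6 months after the last participant has received the results letter".

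**The concern.** Two clocks are in use and they are not reconciled. Costs run from baseline; the data that feed them run from the results letter. The gap is the time needed to collect risk factors, return and batch samples, and produce the report. The article gives no figure for it, but it cannot be zero for women who have PGS testing.

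The healthcare use that matters most for the cost of this pathway comes after the letter: the GP appointment, referral to clinical genetics, and enhanced screening or preventative medication. A window that closes 6 months after baseline closes before the 6-month questionnaire is sent, and the later steps in that sequence are the most exposed. Cost is one of the three kinds of evidence the abstract says the study will provide, and one of the listed objectives, so the period being costed should be unambiguous.

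**Working it through.** The plan gives no numerical figure to reproduce here. The check is window arithmetic on the stated time points.

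**Inputs**
- Costing window: baseline to baseline + 6 months (Economic analysis; text under Table 2).
- Follow-up healthcare-use questionnaire: results letter + 6 months (Table 2 and the text under it; Data collection).
- Lag L, in months from baseline to results letter: not stated, so varied as an assumption.

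**Step 1: where the questionnaire falls.** The letter is at baseline + L, so the 6-month questionnaire is at baseline + L + 6. The costing window ended at baseline + 6, which is L months earlier. No healthcare-use questionnaire coincides with the end of the window unless L = 0.

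**Step 2: window followed as written.** Post-result months costed = max(0, 6 − L).

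| Assumed L (months) | Post-result months costed | Share of the 6 post-letter months |
|---|---|---|
| 0 | 6 | 100% |
| 1 | 5 | 5/6 = 83% |
| 2 | 4 | 4/6 = 67% |
| 3 | 3 | 3/6 = 50% |
| 4 | 2 | 2/6 = 33% |
| 6 or more | 0 | 0% |

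Practices receive a list of women advised to see their GP each month (Risk categorisation and returning risk assessment results). For a woman who has not booked and is prompted from that list, up to about one further month can pass. At L = 3 that leaves about 3 − 1 = 2 months of the window after the prompt.

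**Step 3: questionnaire asks about the last six months instead.** It then covers baseline + L to baseline + L + 6. All post-result months are captured, but the L months between baseline and letter are in neither the baseline recall nor the follow-up recall.

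**Step 4: can the article bound L?** Only loosely. Recruitment closes on 30 June 2025 and results are expected by 31 August 2026, 14 months later. Taking off 6 months of follow-up leaves 14 − 6 = 8 months at most, with nothing allowed for analysis. This does not narrow the range usefully.

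**The case against.** The strongest reply is that the phrase about six months after baseline is loose wording for the 6-month column of Table 2. With a six-month recall at that point, nothing after the letter is lost. The recall wording is not shown, and an article may leave it to the full protocol. This stands as far as it goes: truncation of post-result use follows from one of two readings. But the same paragraph under Table 2 lists baseline and the post-result time points separately, and the baseline window is repeated in Economic analysis. The loose reading also leaves the baseline-to-letter period uncollected by questionnaire, so a mismatch remains either way.

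The second reply is that the later events are recorded elsewhere. This is correct. GP consultation, enhanced screening, medication and surgery are asked about at 1, 3 and 6 months after the result for the women concerned. GP records reach at least 6 months past each woman's letter, and referrals and their outcomes come from the clinical genetics clinic. The fault is therefore in the definition of the costing window, not in data capture, and it can still be corrected at analysis.

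The third reply is that lost months are not lost costs. This also stands. The letter itself advises a GP appointment and practices follow up monthly, so GP contact probably comes soon after the letter. Screening and medication are more exposed.

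Finally, this is a single-group feasibility study, costs are reported descriptively, and cost is not a progression criterion. That limits how much rests on the point.

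**Conclusion.** The inconsistency is real and worth correcting. As written, the costing window covers max(0, 6 − L) months after the result: 5, 4, 3 or 2 months for assumed lags of 1, 2, 3 or 4 months. These figures are illustrative because the article does not state the lag, which may be short for women who decline PGS testing. They describe months of observation, not shares of cost. Delivery of the assessment itself falls before the letter and is largely inside the window.

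A reader might infer three stronger conclusions, none of which the article supports:
- **That post-result costs fall wholly outside the window.** This needs a lag of 6 months or more, and nothing in the article shows one.
- **That the cost-effectiveness model is biased downward.** The article says only that study data will be applied to an existing model. It does not restrict the inputs to these six-month totals, and uptake and referral data are also study data.
- **That costs are biased differently by PGS testing.** Lags plausibly differ, but no cost comparison by PGS status is planned.

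**What to change.** Reconcile the text under Table 2, Data collection and Economic analysis on one set of time origins:

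1. Cost two phases separately: baseline to results letter (delivery) and results letter to 6 months after it (consequence).
2. Take consequence-phase use from the 6-month questionnaire, supplemented by GP records and clinical genetics data. The genetics data are described as practice-level and aggregated, so check whether they can support costs per participant or only totals.
3. Take delivery-phase use from study logs of the assessment process and from GP records.
4. Where 6-month questionnaires have not yet been sent, word the recall period as the time since the results letter. Where they have been sent, state which period was asked about and define the analysis window to match.
5. Make any comparison with the 6 months before baseline per person-month.
6. Report the observed distribution of the lag, so that readers can see how long the delivery phase was.

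The cost is small: wording in the plan and, where still possible, in the questionnaire. The study should already hold the dates of baseline and of the letter, since questionnaires are scheduled from the letter. The one drawback is that the delivery phase varies in length between women, which is why rates per person-month are needed rather than simple totals.
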